## Abstract

**Background:**

Total hip replacement (THR) is the preferred method for the active and lucid elderly patient with a displaced femoral neck fracture (FNF). But controversy still exists regarding using cemented or uncemented stem in these patients. The aim of this study is to compare a cemented and uncemented femoral stem in patients 65–79 years treated surgically with THR for displaced FNF.

**Methods/design:**

In a single-centre, single-blinded, randomized controlled trial, we will include 140 patients aged 65-79 years with an acute displaced FNF and randomize them in a 1:1 ratio to a cemented tapered or a uncemented tapered hydroxyapatite - coated femoral stem. A cemented cup will be used in both groups. The patients will be blinded for allocation. The primary endpoints will be the incidence of all hip-related complications and health-related quality of life evaluated with EuroQol-5D (EQ-5D) index up to 2 years after surgery. Secondary outcomes will be overall mortality, general medical complications and hip function. The follow-up will be at 3 months, 1 and 2 years. Further follow-ups after end of study will be at 4 and 10 years. Results will be analysed using 95 % CI’s for the effect size. A regression model will also be used to adjust for stratification factor.

**Discussion:**

The ethical committee at Karolinska Institutet has approved the study. An interim analysis on the primary endpoints will be performed when half the sample size is included. The results from the study will be disseminated to the medical community via presentations and publications in relevant medical journals. The study will provide evidence if a cemented or uncemented femoral stem is preferable in THR for elderly patients with a displaced FNF.

**Trial registration:**

The trial is registered at clinicaltrials.gov (NCT02247791), October 21, 2013.

## Background

Total hip replacement (THR) is the preferred method for the active and lucid elderly patient with a displaced femoral neck fracture (FNF) [1, 2]. Comparisons between cemented and uncemented stems in hip arthroplasty for patients with a FNF have almost consistently favoured cemented fixation, mainly because of greater deterioration in pain, walking ability, use of walking aids and activity of daily living [3] and because of a higher incidence of hip related complication such as periprosthetic fracture [4] for uncemented implants. Despite this, recent reports on modern, hydroxyapatite-coated femoral stems used for this patient-group have shown promising early results [5-7]. In addition, bone cement implantation syndrome (BCIS), is more prevalent in cemented than in uncemented stems [8]. It is also a commonly occurring phenomenon in patients treated for FNF with cemented arthroplasty and severe BCIS has a significant impact on early and late mortality [9]. Thus, the use of uncemented stems for this patient group may still be justified.

We hypothesized that an uncemented, proximally porous and hydroxyapatite coated femoral stem used in THR for a displaced FNF would not be associated with more adverse peri- and postoperative hip-related complications compared with a THR using cemented stem, and that the health-related quality of life for the patients would be equivalent at 2 years.

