### Sample size and power analysis

Prior to the study start, a sample size calculation was done. To show non-inferiority with 80 % power of the primary endpoint all hip-related complications between the two groups, assuming a total complication rate of 20 %, and with a non-inferiority limit of 15 % requires 60 patients in each group. The assumed 20 % complication rate includes also minor hip-related complications as per previously published papers ranging between 10 and 20 % [1, 2, 6]. To show non-inferiority with 80 % power of the primary variable health related quality of life – HRQoL, as measured with EQ-5D requires 40 patients in each group, and with a non-inferiority limit of 0.1, assuming a value of 0.73 (SD 0.18) 1 year after the surgery [5]. The alpha (2-tailed) is set at 0.025 since we have two endpoints for the power calculation. Since this patient group has a 1-year mortality of 10 %, 70 patients in each group should be sufficient for the study.

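### The quality-of-life hypothesis says equivalent, but EQ-5D is sized only for non-inferiority, and neither hypothesis nor test refers to the stated limits

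*Protocol article*

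**What the plan says.** All places are in the protocol article.

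- **Background, hypothesis on complications.** An uncemented stem "would not be associated with more adverse peri- and postoperative hip-related complications compared with a THR using cemented stem".
- **Background, hypothesis on quality of life.** The same sentence continues "and that the health-related quality of life for the patients would be equivalent at 2 years".
- **Sample size and power analysis, complications.** The calculation is made "To show non-inferiority with 80 % power of the primary endpoint all hip-related complications between the two groups". Its inputs are a 20 % complication rate and a 15 % limit.
- **Sample size and power analysis, EQ-5D.** The calculation is made "To show non-inferiority with 80 % power of the primary variable health related quality of life", with a limit of 0.1, an assumed value of 0.73 (SD 0.18) at 1 year, and 40 patients per group. Alpha is 0.025, described as 2-tailed because there are two endpoints. The final size is 70 per group, allowing for 10 % mortality at 1 year.
- **Analysis.** Fisher's exact test is named for the primary endpoint, and Student's t-test and Levene's test for the functional outcomes, with 95 % intervals. The abstract also plans 95 % intervals for the effect size. Neither place mentions a limit.
- **Abstract, Discussion.** The closing sentence reads "The study will provide evidence if a cemented or uncemented femoral stem is preferable in THR for elderly patients with a displaced FNF".

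**The concern.** Equivalence and non-inferiority are different claims. Equivalence requires the difference to be bounded on both sides; non-inferiority bounds it only on the side where the uncemented stem is worse. The Background asserts equivalence for EQ-5D, and the sample size section provides for non-inferiority.

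The analysis text does not settle which applies, because the tests it names are tests of difference and do not use a limit. A non-significant result could then be read as confirming the hypothesis as worded: equivalent quality of life, or no more complications. Absence of a significant difference supports neither statement. At stake is what may be concluded from the trial, and whether that is fixed before the results are known.

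**Working it through.** **Inputs from the sample size section:** SD 0.18, limit 0.1, power 80 %, two-tailed alpha 0.025 (0.0125 in each tail), 70 per group, 10 % mortality at 1 year, complication rate 20 %, limit 15 %.

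**Assumptions:** 63 evaluable per group (70 × 0.9; attrition at 2 years is not given); true difference 0; equivalence range ±0.1, since none is stated; SD 0.18, a 1-year figure, applied to the 2-year comparison; 15 % read as percentage points and 20 % as the rate in each arm.

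**1. The plan's own EQ-5D figure.** For non-inferiority, n per group = 2 × SD² × (z₁₋ₐ + 0.842)² / limit², where a is the one-sided level and 2 × 0.18² / 0.1² = 6.48.

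- a = 0.0125: 6.48 × (2.241 + 0.842)² = 61.6, so 62.
- a = 0.025: 6.48 × (1.960 + 0.842)² = 50.9, so 51.
- a = 0.05: 6.48 × (1.645 + 0.842)² = 40.1, so 41.

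The stated 40 is matched, within rounding, only at one-sided 0.05 and not at the stated alpha. The point here does not rest on that, because 63 evaluable patients are expected.

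**2. EQ-5D power at 63 per group.** SE = 0.18 × √(2/63) = 0.0321, and 0.1 / 0.0321 = 3.12. Non-inferiority power = Φ(3.12 − z). Equivalence power, with both bounds required, = 2 × Φ(3.12 − z) − 1.

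| Interval | z | Non-inferiority | Equivalence within ±0.1 |
|---|---|---|---|
| 97.5 % (two-tailed 0.025) | 2.241 | Φ(0.88) = 81 % | 2 × 0.810 − 1 = 62 % |
| 95 % | 1.960 | Φ(1.16) = 88 % | 2 × 0.877 − 1 = 75 % |

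With all 70 per group evaluable, equivalence power would be 70 % and 82 %; with 60 it would be 58 % and 72 %.

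**3. Size needed for equivalence at 80 % power.** n = 6.48 × (z₁₋ₐ + 1.282)², because the 20 % type II error is split between two bounds.

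- a = 0.0125: 6.48 × 3.523² = 80.4, so 81 per group.
- a = 0.025: 6.48 × 3.242² = 68.1, so 69 per group.

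**4. What a non-significant difference test would mean for complications.** Suppose the true rates are 20 % and 35 %, an excess exactly at the limit. With 63 per group and the normal approximation for two proportions, power to detect that difference is 36 % at two-sided 0.025 and 47 % at 0.05. The test would be non-significant in 64 % or 53 % of such trials. By contrast, requiring the interval to lie below 15 points would wrongly pass in only about 1.25 % or 2.5 % of them.

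**The case against.** Much can fairly be said for the plan.

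- **A reader might infer that a successful trial could never support its hypotheses, or that the design is one-sided.** The article does not support this. It states a two-tailed alpha and plans two-sided intervals. An EQ-5D interval lying wholly inside ±0.1 would show equivalence within that range, and an interval excluding zero would show that one stem is better. These outcomes are possible; equivalence is simply not what the trial was sized for.
- **A reader might infer that the complications hypothesis contradicts the design.** It does not. Saying that a treatment is not associated with more complications is ordinary non-inferiority wording and agrees in direction with the sizing. It lacks only the limit.
- **A reader might infer that the design accepts a 15-point excess.** A margin is the excess the interval must exclude. At 63 per group and 20 % in each arm, the half-width is 1.96 × √(0.32/63), about 14 points, so with 95 % intervals the observed excess could be only about 1 point.
- **A reader might call the limits wide.** For EQ-5D the article gives no minimal important difference, so this cannot be judged.
- **A reader might treat the promise to show which stem is preferable as a third objective.** It is a closing remark. The stated aim is to compare the stems.
- **A reader might expect opposite verdicts on the same data.** That needs a defined equivalence criterion, and there is none; ±0.1 is an assumption of this check.

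It can also be said that *equivalent* was used loosely and that a full protocol or analysis plan may define the rule. Loose use is plausible, but the hypothesis and the sizing stand in the same document and differ. The named tests do not resolve the difference.

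**Conclusion.** The point holds in a limited form. The EQ-5D hypothesis is worded as equivalence while the endpoint is sized for non-inferiority. Under the assumptions above, the hypothesis as worded has about 62 % power at the stated alpha, or 75 % with 95 % intervals, against 81 % or 88 % for non-inferiority. It would reach 80 % only with 95 % intervals and almost no loss of patients (69 evaluable per group needed, 70 randomized). The complications hypothesis is consistent in direction but should carry its 15-point limit, and the planned tests should be tied to both limits.

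This is a mismatch of claim, sizing and conclusion rule. It does not mean that the trial is incapable of an informative result, and it is not a judgement that either limit is too large. The size of the mismatch rests on the assumed ±0.1 range, a true difference of 0, and 63 evaluable per group.

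**What to change.** 1. In the Background, replace *equivalent* by non-inferiority within the stated limits: the uncemented stem is not worse than the cemented stem by more than 0.1 on EQ-5D, nor by more than 15 percentage points on hip-related complications. Keep the endpoint definitions given under Primary endpoints.
2. In the Analysis section, state that the conclusion on each primary endpoint is drawn by comparing the confidence interval with the limit at the stated alpha. Two-tailed 0.025 corresponds to a 97.5 % interval, whereas the text speaks of 95 %, so the level must be written into the rule.
3. State that meeting the limit supports only *not worse by more than the limit*, and that a non-significant difference test supports neither *equivalent* nor *not more*.
4. State that one stem is called better on an endpoint only if the same interval also excludes zero.
5. Align the closing sentence of the abstract's Discussion with this rule.

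The cost is wording and a more modest claim. No extra patients, visits or data are needed. If equivalence is truly wanted, a range must be defined and, for ±0.1 at the stated alpha, 81 evaluable patients per group would be needed.

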## Methods/design

### Trial design, settings and location

This single centre, single-blinded, prospective randomized controlled trial will be performed between 2009 and 2025 at the Orthopaedic department Danderyd Hospital, Stockholm, Sweden. Danderyd Hospital is an emergency regional teaching hospital affiliated with the Karolinska Institute and has a catchment area of approximately 500,000 inhabitants. The guidelines of Good Clinical Practise (ICH-GCP) will be followed [10]. The Local Ethics Committee at Karolinska Institute approved the protocol. The guidelines of the CONSORT Statement will be followed [11] for the final paper and the SPIRIT guidelines for the study protocol [12].

### Randomization and blinding

The patients will be block-randomized in a 1:1 ratio, to receive either cemented or uncemented stem. We will use sealed envelopes and randomization will be stratified by sex to ensure that the sex distribution will be the same in both groups. The study subjects will be blinded to choice of treatment. To verify that the blinding is maintained during the study, the patients will be asked if they knew their assigned allocation arm at the 2-year follow-up. The surgeons and staff are not blinded during the study.

### Study subjects and eligibility criteria

All patients with a displaced FNF who are admitted to Danderyd Hospital will be screened for participation in the study. Research nurses who identify eligible patients before surgery screen all patients at arrival to the hospital. The first author ([name]) or one of the other co-authors will include patients and acquire informed consent. All who agree to participate and give their oral and written informed consent will be included if they fulfil the inclusion criteria. The inclusion criteria are an acute (within 48 h) displaced FNF (Garden III to IV) [13] after a low-energy trauma (i.e. fall), an age 65–79 years, no concurrent joint disease or previous fracture in the lower extremities, an intact cognitive function (no diagnosis of dementia and at least seven correct answers on a ten-item Short Portable Mental Status Questionnaire [14], ability to ambulate independently with or without the help of walking aids. The age limits for THR (65–79 years) are standard in our hospital and in most Swedish hospitals. We will exclude patients with pathological fractures, and those with rheumatoid arthritis or symptomatic osteoarthritis of the hip. We will also exclude those who, because of severe co-morbidities, are deemed not suitable for a THR by the anaesthesiologist, and those who are unsuitable to participate in the study for any other reason (substance abuse, alcoholism). Based on our previous experience in randomized clinical trials in this population, [1, 5] we expect to include and receive informed consent from approximately half of the target population (i.e. 65–79 years and fulfilling other inclusion criteria).

The baseline data of the patients’ health-related quality of life and hip function will be obtained retrospectively for the last week.

### Surgical intervention

Surgery in both groups will be performed by a consultant or a specialist experienced in both procedures using a direct lateral approach [15] with the patient in the lateral decubitus position. Preoperative planning will be performed using digital software (MDesk; RSA Biomedical AB, Umeå, Sweden). The modular CPT (Zimmer, Warsaw, Indiana, USA) collarless, polished, tapered femoral component manufactured from cobalt-chromium will be used used in the cemented group. The Bi-Metric stem (Biomet, Warsaw, Indiana, USA) is a tapered, proximally coated (plasma-sprayed, commercially pure [CP]) titanium femoral stem and will be used in the uncemented group. A 32 mm cobalt-chromium will be used for all patients.

In the acetabular component we will use a cemented XLPE cup and a vacuum-mixed low-viscosity cement with gentamicin. All surgeons have a long experience with all implants so no learning curve is expected. Low-molecular-weight heparin (Fragmin, Pfizer, Täby, Sweden) postoperative day 1 and for at least 10 days postoperatively will be given as thromboprophylaxis. Antibiotic prophylaxis with Cloxacillin 2 g (Ekvacillin; Meda Sweden) will be given preoperatively, followed by two additional doses during the first 24 h. Patients in both groups will be mobilised with full weight bearing with the aid of two crutches as tolerated and to abandon crutches at their own convenience. After 6 weeks they will be permitted to mobilise without further restriction. A physiotherapist will follow all patients for the first 3 months after surgery.

### Outcome measurements

#### Primary endpoints

The primary endpoints will be 1) the incidence of all hip-related complications up to 2 years after surgery and 2) change in health-related quality of life assessed with EQ-5D index (EuroQol) [16] up to 2 years. Hip-related complications are defined as intra- and postoperative periprosthetic fractures, dislocation, wound infection both superficial and deep, loosening both early and late and revision of any prosthetic implant for any reason.

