### Data collection and follow-ups

The primary assessment will establish that the patient fulfils all inclusion/exclusion criteria and identify any comorbidity. The patients will then be interviewed by a research nurse regarding living conditions, mobility, activities of daily living (ADL) [22], status and health-related quality of life according to the EQ-5D during the last week before the fracture as a baseline. For all primary and secondary endpoints including ADL the patients themselves will be providing data during the study period. It is obvious that the patients’ ability to record this correctly while awaiting urgent surgery may be questioned. It is, however, impossible to collect these data in a prospective manner and the method is regularly used in patients with a fracture of the hip [1, 2, 19]. Patients who are unable or unwilling to attend follow-ups will be interviewed by telephone or they will send their answers by mail. We will use the unique Swedish personal id-number and collect data prospectively throughout the study period through a combination of a search of our databases, follow-ups and the Swedish Hip Arthroplasty Register. Non hip-related adverse events (AEs) and serious adverse events (SAEs) will be collected throughout the study period (2 years). Although the primary endpoints will be evaluated at 2 years, the study will also include a 4 and 10-year follow-up. The study visits are presented in Table 1.

**Table 1 Tab1:** All visits in the study

	d 0	d 0	0	+1 d	+4 d	5d	3 m.	1 y	2 y	4 y	10 y
	Screening	Inclusion	Randomization and surgery	POD1	POD4	End of In-pt stay	Follow-up	Follow-up	Follow-up	Follow-up	Follow-up
Screening for eligibility	x										
Informed consent		x									
Baseline data		x									
Randomization			x								
X-ray	x			x				x	x	x	x
HHS		x						x	x	x	x
VAS		x						x	x	x	x
EQ-5D		x						x	x	x	x
Adverse events			x	x		x	x	x	x	x	x
Intraoperative			x								
Blood test		x		x	x		x				

X-ray = anterioposterior and lateral radiographs, HHS = Harris hip score, EQ-5D = Quality of life score, Intraoperative = Intraoperative measurements including blood pressure, puls rate, pulse oxyometry before, during and after femoral stem insertion, VAS = Visual Analogue Scale for hip pain, Bloodtest = C-reactive protein (CRP), IL-6, Hb, D-dimer

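### The EQ-5D primary endpoint is defined as a change, but the hypothesis concerns the 2-year level and the sample size uses the SD of a 1-year level, so the stated power does not carry over to the endpoint as defined

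*Protocol article*

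**What the plan says.** The protocol article describes the EQ-5D co-primary in several places.

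- **Primary endpoints:** "change in health-related quality of life assessed with EQ-5D index (EuroQol) [16] up to 2 years". The reference point of the change is not named.
- **Study subjects and eligibility criteria:** "The baseline data of the patients’ health-related quality of life and hip function will be obtained retrospectively for the last week".
- **Data collection and follow-ups:** patients are interviewed about "health-related quality of life according to the EQ-5D during the last week before the fracture as a baseline". Table 1 shows no other EQ-5D before surgery. The same section concedes: "It is obvious that the patients’ ability to record this correctly while awaiting urgent surgery may be questioned". It also places the evaluation of the primary endpoints at 2 years.
- **Background (hypothesis):** "the health-related quality of life for the patients would be equivalent at 2 years". This is a level, not a change.
- **Sample size and power analysis:** 80% power with 40 per group, "with a non-inferiority limit of 0.1, assuming a value of 0.73 (SD 0.18) 1 year after the surgery", at a two-tailed alpha of 0.025. This too is a level, and at 1 year. The total is set at 70 per group to allow for 10% 1-year mortality.
- **Abstract, Methods/design:** "health-related quality of life evaluated with EuroQol-5D (EQ-5D) index up to 2 years after surgery". The word change does not appear.

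The Analysis section plans a t-test for functional outcomes without saying whether it acts on the level or the change. No SD of change, baseline SD or baseline-to-follow-up correlation is given.

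**The concern.** A change score and a follow-up value are different variables with different SDs. The planning SD of 0.18 describes a value. If the change is what is tested against the 0.1 limit, 0.18 is the right SD only by coincidence, and the power printed for this co-primary belongs to another variable.

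The baseline makes this more than a matter of wording. It is a recollection of the pre-fracture state, collected while the patient awaits urgent surgery, and a fracture and an arthroplasty lie between it and the 2-year measurement. A low correlation is conceivable, though not documented, and in that case subtracting the baseline adds more noise than it removes.

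With both definitions in print, it is also open which of two estimates is held against the limit. In a single trial they can differ, and non-inferiority on a co-primary could turn on the choice.

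**Working it through.** **Inputs from the article.** Limit 0.1; SD of the post-operative value 0.18; power 80%; two-tailed alpha 0.025, that is 0.0125 on the one side that matters for non-inferiority; 40 per group stated as required; 70 per group planned; 10% 1-year mortality, so 70 × 0.9 = 63 per group.

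**Assumptions, not in the article.** True difference 0; baseline SD also 0.18; r from 0.2 to 0.7.

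**Step 1: the plan's own figure.** For a value, n per group = 2 × [0.18 × (z₁₋α + z₀.₈) / 0.1]².

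- One-sided 0.05: 40.06, so 40 to 41.
- One-sided 0.025: 50.9, so 51.
- One-sided 0.0125 (the stated alpha): 61.6, so 62; 63 with the noncentral t distribution.

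The stated 40 is reproduced only at one-sided 0.05. At the stated alpha, 40 per group gives about 58% for the value (noncentral t). With 63 per group the value has 80%.

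**Step 2: SD of a change.** With equal SDs, SD_change = 0.18 × √(2(1 − r)). This equals 0.18 at r = 0.5, is larger below and smaller above.

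**Step 3: SD after baseline adjustment.** SD_adj = 0.18 × √(1 − r²), never larger than 0.18. It is also never larger than SD_change, because 1 − r² = (1 − r)(1 + r) ≤ 2(1 − r).

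**Step 4: power at 63 per group**, limit 0.1, two-tailed 0.025, noncentral t:

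| r | SD of change | Power, change | n per group for 80%, change | SD adjusted | Power, adjusted 2-year value |
|---|---|---|---|---|---|
| 0.2 | 0.228 | 58% | 100 | 0.176 | 82% |
| 0.3 | 0.213 | 64% | 88 | 0.172 | 84% |
| 0.5 | 0.180 | 80% | 63 | 0.156 | 91% |
| 0.7 | 0.139 | 96% | 39 | 0.129 | 98% |

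**Step 5: sensitivity.**

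- *Alpha.* At one-sided 0.025, power for change with 63 per group is 69% at r = 0.2 and 74% at r = 0.3, against 87% for the value. The mismatch does not depend on how alpha is read.
- *Baseline SD.* If it is 0.22 or 0.25 instead of 0.18, then at r = 0.5 the SD of change is 0.203 or 0.223, and power at 63 per group is about 69% or 60%.
- *Attrition.* The figure of 63 reflects 1-year mortality only. If 15% to 20% were missing at 2 years (assumed; 59 or 56 per group), power for the unadjusted value would be about 77% or 75%.

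**The case against.** The strongest reply is that the harm hangs on a correlation the article does not report. Above r = 0.5 the change score is the more powerful variable. A reader might infer from the low-r rows that the trial is underpowered for this endpoint. The article does not support that: it gives no r, so the direction of the error is open.

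A reader might also infer that the printed power claim would be sound if the endpoint were simply the value. It would not be. At the stated alpha, 40 per group falls short for the value too (Step 1). That is a separate fault, and rewording the endpoint does not cure it.

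A third tempting reading is that chance imbalance in recalled baselines harms only the change score. One standard error of a baseline difference is 0.18 × √(2/63) = 0.032. But given a baseline difference d, the unadjusted value is expected to shift by r × d and the change by (1 − r) × d in the opposite direction. With d = 0.03 and r = 0.3 these are 0.009 and 0.021; at r = 0.5 they are equal in size. Under randomisation both variables have the same expected group difference, so the 0.1 limit means the same for either.

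Finally, the recall problem is disclosed and prospective collection is said to be impossible, the abstract's wording may be mere shortening, and a separate analysis plan may settle which variable the t-test uses. All fair. What stands is that the endpoint definition, the hypothesis and the sample-size basis are all printed in this article and do not describe the same variable.

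**Conclusion.** The point holds as an inconsistency in the definition and sizing of one co-primary endpoint. The endpoint is a change, the hypothesis is about the level at 2 years, and the SD is that of a level at 1 year. The stated power carries over to the endpoint as defined only if the SD of change is near 0.18. Across the assumed range of r, power for change at 63 per group runs from 58% to 96%, so the consequence may be a loss or a gain.

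This rests on four things: that the change is measured from the recalled pre-fracture EQ-5D, which is inferred because no other pre-operative measurement exists; equal SDs of 0.18; a true difference of zero; and 63 evaluable patients per group, which allows for 1-year mortality only. It should be corrected, but it does not show that the trial is too small.

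**What to change.** In Primary endpoints, define the second endpoint as the EQ-5D index at 2 years, in line with the hypothesis and the stated time of evaluation. Compare the groups with a linear model that has the recalled baseline EQ-5D as covariate (ANCOVA), apply the 0.1 limit to the adjusted difference, and report change from baseline descriptively. Recall error in a covariate reduces the gain in precision, but it is not subtracted into each patient's outcome.

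In Sample size and power analysis, restate the EQ-5D power at the stated alpha, with the number expected to be evaluable at 2 years, and say that the SD is a 1-year figure. If change is kept as the primary variable, base the power on an SD of change over a stated range of r.

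The cost is a reworded endpoint, a small amount of extra analysis and a restated power figure. No new data are needed, because the baseline EQ-5D is already collected. Apart from one degree of freedom, the adjusted analysis loses no precision against the unadjusted value or the change score.
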